#### Setting and sample size

The research setting is a petrochemical industry in Iran. The study population consists of workers of this Iranian petrochemical company. Since this study aims to promote workers’ safe behaviour, as reported by Waters and Duncan [47] (a similar study), the effect of the behavioural safety program interventions that is considered as the dependent variable in this study has been 40%, if it is assumed that environmental factors and non-compliance by control group participants account for about 50% of this effect, namely 20%, for each group, based on the following formula [48] and with 95% confidence interval and 80% power of a test, 78 participants will be required.. The researcher will hypothesize a 10% attrition rate (in both groups). In order to ensure that the total sample size is available, the researcher will need to recruit more participants to allow for attrition. Therefore, with the anticipated attrition rate, the researcher should enrol 176 participants. The participants will be randomly allocated to the intervention group (*n* = 88) or the control group (*n* = 88).$$ {\displaystyle \begin{array}{c}n=\frac{{\left({Z}_{1-\alpha 2}+{Z}_{1-\beta}\right)}^2\left({P}_1\left(1-{P}_1\right)+{P}_2\left(1-{P}_2\right)\right)}{{\left({P}_1-{P}_2\right)}^2}\\ {}=\frac{{\left(1.96+0.84\right)}^2\left(0.4(0.6)+(0.2)(0.8)\right)}{{\left(0.4-0.2\right)}^2}=78.4\end{array}} $$

### Measure

This study is Mixed Methods Research (MMR), in which the research methodology will be presented as follows:Conducting qualitative research;Conducting a literature search to identify theoretical models that have been used to explain and predict safe behaviour in the workplace, both in the petrochemical industry and more generally, and selecting a theoretical model that provides a suitable organising structure for each of the phases of research – quantitative phase, survey, and RCT;Conducting a randomised controlled trial (RCT) to assess the effectiveness of the intervention.

### Phase one: qualitative exploration

#### Approach to interviewing

Semi-structured interviews will be conducted to gain in-depth understanding of factors associated with unsafe work behaviour in the company. Probing questions will be used when answers are vague or ambiguous or to obtain more specific or in-depth information. Conducting the interviews and analysis of the qualitative data will occur through an iterative process, such that data from earlier interviews will be allowed to influence the content of later interviews. All respondents will be asked identical questions in the same sequence, but the interviewer will probe inductively on key responses. Sometimes the respondents will provide information on new areas and these will be included in subsequent interviews. This process enables the researcher to gain deeper insight into the data, while continuing the data collection [49]. Data will be collected until no more new themes emerge from the data and the interviewer is confident that data saturation has been achieved [50, 51].

#### Data collection

The interviews will be conducted in the period May – July 2017 at mutually convenient and private areas at the participants’ workplaces. The interview questions will be classified into three categories:What are your individual feelings or perceptions of being safe at work?Have you experienced workplace accidents directly yourself or have you witnessed accidents by your colleagues in the workplace?What are the main factors contributing to the occurrence of workplace accidents?

The interviews will be audiotaped and a summary of the key issues in each interview will be then sent to each participant to ensure that the researcher will have accurately interpreted that participant’s comments (a ‘member check’) [52]. All interviews will be then transcribed in Persian and translated into English for qualitative analysis. Any identifying information in the transcripts will be removed prior to data coding.

#### Data analysis

Conventional content analysis will be used to interpret the content of text data through a systematic classification process involving coding and identifying themes [53]. Open coding will be carried out to allow codes to emerge from the qualitative data and avoid codes based on predispositions of the authors. Immersion in the data is an important first stage in the analysis process during which transcripts will be read and re-read many times to become completely familiar with the data. Repeated reading and re-reading of transcripts without coding helps identify emergent themes from the data without losing the connections between key concepts and their context. Content analysis will be performed using MAXQDA (Ver. 2018) software to facilitate and document the coding process and retrieve codes afterwards. It should be noted that while software can assist researchers to organise qualitative data, computer software for qualitative analysis does not analyse data and the researcher makes decisions about coding participants’ responses, and the relationships between codes, coding categories and broader themes. MAXQDA allows the researcher to upload raw data, such as transcribed interviews, that then can be coded and cross-referenced in ways that facilitate organising the data for easy retrieval.

This study will employ the approach to qualitative content analysis described by Graneheim and Lundman [54]. This approach consists of the following elements: units of analysis, meaning units, condensation of meaning units, and development of codes, categories and themes. One of the most basic decisions when using content analysis is selecting the unit of analysis. Whole interviews or observational protocols are considered to be units of analysis. In the second step, the interview text is divided into smaller units called meaning units. A meaning unit — which could be words, sentences or paragraphs — contains aspects, words or statements that relate to the same central meaning. In the third analysis step, condensation, units are shortened while still preserving their core meaning. In the fourth step, codes are developed as descriptive labels for the meaning units. They are tools to help researchers reflect on the data in new and different ways. The fifth step is to sort codes into categories that answer the question, “What?”. In other words, a category is formed by grouping together those codes that are associated with each other through their content or context and belong together. A theme can be seen as expressing the underlying meanings together in two or more categories. The final step of data analysis is the creation of themes. A theme answers the question, “How?”. Therefore, theme names include verbs, adverbs and adjectives and are very descriptive.

### Phase two: questionnaire survey

A variety of conceptual models of workplace safety have been developed to help organise research findings and guide the development of occupational safety programs [55–57]. These models are useful because they highlight the importance of workers’ job characteristics, the job tasks being performed and the organisational structure. These models have been applied to raise workers’ awareness of occupational hazards and encourage them to adopt safe behaviour [58, 59].

In present study, theoretical models which have been applied to explain and predict safe behaviour in industrial settings, more generally and in parallel, and theoretical models that have been developed or applied in the petrochemical companies will be investigated. Findings that emerge from the qualitative phase will then be employed to identify the best model fits the data. In regard to the model components, questionnaires will be designed/ developed to conduct a pre-test survey. Based on information obtained from this, educational needs assessment will be conducted and then an educational intervention will be designed in order to train workers.

#### Questionnaires

The questionnaire will consist of two parts. The first part will cover social demographics and the second part will include the constructs of the conceptual model. Data will be collected at baseline, after the intervention, and after three months for workers from the intervention group and the control group. The questionnaires will be anonymous to promote participation and workers’ confidence in the intervention. All the participants who will be doing measurements will be blinded to the assigned groups of the study.

### Phase three: randomised controlled trial (RCT)

The randomised controlled trials (RCTs) is the basic methodological paradigm for the evaluation of public health interventions. RCTs aim to generate that the assignment of study subjects to the intervention or the control group is exclusively due to chance, thus avoiding effects of confounding and selection biases. The availability of a control group makes it possible to distinguish between epidemiological and/or statistical associations and cause-effect relations [60]. The RCT design is a significant strength of this study, including qualitative and quantitative measures to assess the effectiveness of the intervention.

#### Intervention

The intervention will include multiple components associated with information obtained from pre-test stage and constructs of the conceptual model. Participants will attend eight weeks of biweekly 90-min intervention sessions. Each session will consist of two parts, a 60-min interactive workshop followed by a 30-min group activity. There will be different themes for each of the workshops, which will start with a presentation to highlight the important factors, and effective strategies for changing unsafe behaviour to overcome barriers they may have encountered and discussions between workers and the researcher. Then, each workshop will be followed by group activities. All video and written teaching materials for these sessions will be prepared by the research team. One important goal of the workshops is to teach workers how to identify workplace hazards, to promote their own safe behaviour and maintain it. In the second part of the intervention, texts and messages related to different aspects of workplace safety will be sent to the participants in the intervention group via WhatsApp. Apart from the workshops, there will be two consultation sessions with managers and supervisors during the intervention period. These sessions will prompt them to be fully committed to safety issues so that top prioritisation of safety will be widely accepted. Finally, educational software (multimedia) will be designed. Participants allocated to the control group will be asked to attend measurement sessions, but they will only receive the intervention six months later (i.e., after the follow-up time point).

Analyses will be conducted using SPSS Ver.24 and alpha levels will be set at *p* > 0.05. Descriptive statistics will be applied to describe the study population at baseline. The categorical variables will be analysed using frequency distribution description and centralised trend description. The continuous variable will be analysed using means ± standard deviations. The difference of characteristics of participants will be compared by t test or chi-square 2 test or non-parametric equivalent test. Effectiveness of the intervention will be measured by the differences between the study groups (intervention group and control group). To provide a more comprehensive analysis of the theoretical relationships among the factors in the conceptual model, path analysis techniques will be applied with AMOS Ver.24. Qualitative data from semi-structured interviews will be processed using MAXQDA (Ver. 2018).

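### The 80% power assumes independent workers, although the intervention arm alone is taught in workshop groups; any positive within-workshop correlation puts it below 80%

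*Protocol article*

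**What the plan says.** **Allocation.** Under Setting and sample size, individual workers are the unit of randomisation: "The participants will be randomly allocated to the intervention group" or to the control group, 88 in each.

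**Delivery.** The Intervention section describes eight weeks of sessions for the intervention arm: "Each session will consist of two parts, a 60-min interactive workshop followed by a 30-min group activity". The workshops also include discussion among workers. Controls attend for measurement only and are offered the programme after follow-up.

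**Size.** The calculation states that "with 95% confidence interval and 80% power of a test, 78 participants will be required". Its variance term is "0.4(0.6)+(0.2)(0.8", which is the sum of two independent binomial variances. The only enlargement is for dropout: "The researcher will hypothesize a 10% attrition rate (in both groups", and so "the researcher should enrol 176 participants". No ICC or design effect appears.

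**Analysis.** The closing analysis paragraph of the Intervention section says: "The difference of characteristics of participants will be compared by t test or chi-square 2 test or non-parametric equivalent test". For effectiveness it refers only to differences between the two study groups and names no outcome test, model or interval method.

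**Data.** The Questionnaires section makes the questionnaires anonymous.

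**The concern.** Workers who share workshops, discussion and group tasks aimed at changing behaviour can be expected to end up more alike than workers who do not. Controls have no such shared exposure. The design is therefore partially nested: independent observations in the control arm, clustered ones in the intervention arm. A formula built on independent binomial variances understates the variance of the between-arm difference in that setting, and 176 workers then provide less power than stated.

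This is not a detail left for a later document. The sizing is complete in the article, and its assumption does not match the delivery described a few sections later. A later analysis plan could correct the standard error but could not restore the missing power.

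The second thing at stake is the standard error itself. If outcomes were analysed as though workers were independent, false-positive risk would exceed the nominal level and intervals would be too narrow.

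**Working it through.** **1. Inputs from the article.** Two-sided alpha 0.05 (z = 1.96); power 80% (z = 0.84); rates 0.40 and 0.20; attrition 10%; 88 per arm.

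**2. The plan's own figure.**
- n per arm = (1.96 + 0.84)² × (0.24 + 0.16) / 0.20² = 7.84 × 0.40 / 0.04 = 78.4.
- Attrition: 78.4 / 0.9 = 87.1, rounded up to 88 per arm and 176 in total.

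Both figures reproduce, for independent workers. With 79 analysed per arm, power is 80.3%, so there is no reserve.

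**3. Inputs that must be assumed.** Group size m and within-workshop ICC ρ are not stated. I take m = 11 to 22 (eight or four groups out of 88), ρ = 0.01 to 0.05, and membership that stays fixed across sessions. Here m is the number analysed per group.

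**4. Variance inflation.** Only the intervention-arm variance is multiplied by 1 + (m − 1)ρ. Reading the intervention arm as the 0.40 arm, as the article implies, its share of the variance is 0.24 / 0.40 = 0.6. Hence

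inflation = 1 + 0.6 (m − 1)ρ, and power = Φ(2.80 / √inflation − 1.96).

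| m | ρ | inflation | power (normal) |
|---|---|---|---|
| 11 | 0.01 | 1.06 | Φ(0.760) = 77.6% |
| 11 | 0.05 | 1.30 | Φ(0.496) = 69.0% |
| 22 | 0.01 | 1.126 | Φ(0.679) = 75.1% |
| 22 | 0.05 | 1.63 | Φ(0.233) = 59.2% |

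Groups of 10 and 20 with 79 analysed per arm give a similar range: 78.2% (m = 10, ρ = 0.01) down to 61.1% (m = 20, ρ = 0.05). Equal arms with 10% attrition would need 184 and 274 enrolled in those two cases, against 176.

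**5. Few groups.** Normal quantiles flatter the result. A Satterthwaite approximation with k groups is df = (v₁ + v₂)² / [v₁²/(k − 1) + v₂²/(n − 1)].
- Eight groups of 11, ρ = 0.05: v₁ is proportional to 0.24 × 1.5 = 0.36 and v₂ to 0.16, so df = 0.52² / (0.36²/7 + 0.16²/87) ≈ 14. Power from the noncentral t is about 63%.
- Four groups of 22, ρ = 0.05: df ≈ 5 and power is about 44%.

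These are rough, but they show that 69% and 59% are upper figures.

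**6. Error rate if workshop group were ignored.** Error = 2[1 − Φ(1.96 / √inflation)].
- Inflation 1.06 gives 5.7%; inflation 1.63 gives 12.5%.
- These use the planning variances. Under an exact null the two arms have equal variance and the intervention share is 0.5. The inflation is then 1.05 to 1.525 and the error 5.6% to 11.3%.

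**The case against.** **The analysis is not fixed.** A reader might infer that the plan commits to t and chi-square tests on the outcomes, so that its intervals will be too narrow. The text does not support this. It attaches those tests to participant characteristics and names no outcome model, which may properly be left to an analysis plan that is not shown. This objection stands, and it makes the error-rate figures conditional.

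**The group structure is assumed.** The article gives no number or size of groups and does not say whether membership is stable, and an article may leave such logistics to the full protocol. If membership rotates, a simple nested model does not fit. With one or two groups the workshop effect can hardly be estimated. At the low end (m = 11, ρ = 0.01) the loss is only about 2 percentage points. All of this limits how firmly a size can be stated. It does not change the direction for any ICC above zero.

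**A full design effect on all 176 would be excessive.** Correct: controls share no workshops, and the calculation above leaves their variance alone.

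**Baseline adjustment might recover the loss.** It might, but that requires linking each worker's responses over time, and the questionnaires are described as anonymous. The usual variance reduction from adjustment is also a result for continuous outcomes, whereas the sizing is for two proportions. The offset cannot be counted on as the article stands.

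**Conclusion.** The sizing point holds. The stated calculation is arithmetically correct for independent workers, but that is not how the intervention arm is treated, and the 80% is overstated for any positive within-workshop ICC. The true figure cannot be derived from the article. Under the assumed ranges it runs from about 78% to 59% with normal quantiles, and lower when the small number of groups is respected. These figures rest on stable groups of 11 to 22, an ICC of 0.01 to 0.05, and the intervention arm being the 0.40 arm.

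The inference point holds only conditionally. If the eventual outcome analysis ignores workshop group, a nominal 5% test would have an error rate of about 5.7% to 12.5% with the planning variances. The article does not say that it will. The point is worth acting on early because workshop membership may be unrecoverable if it is not recorded at data collection.

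**What to change.** - **Data.** Carry a workshop-group code on each intervention worker's questionnaire, with a pseudonymous identifier linking the three time points, and reconcile this with the stated anonymity.
- **Analysis.** Fit outcomes with a partially nested model: a random effect for workshop group in the intervention arm only, controls as singletons, and a small-sample correction such as Satterthwaite degrees of freedom. If very few groups are planned, say how the workshop effect will be handled.
- **Power.** State the planned number and size of groups and an assumed ICC, and replace the unqualified 80% with a matching figure. One example is *at most about 69% at groups of 11 and ICC 0.05*. Do not claim that baseline adjustment offsets the loss unless responses are linked.

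The cost is one extra code, a linking identifier and one model term. The interval becomes somewhat wider and the stated power less favourable. If 80% is to be kept, enrolment has to rise, to between 184 and 274 over the groups of 10 to 20 and the ICC range examined.

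### The significance threshold is printed with the inequality reversed (p > 0.05), against the two-sided 5% level used for the sample size

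*Protocol article*

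**What the plan says.** The protocol article gives a significance level in two places.

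- **Analysis paragraph** (last paragraph of the Intervention section, under Phase three). After naming the software, it states that "alpha levels will be set at *p* > 0.05". The paragraph goes on to say that effectiveness will be judged by comparing the two study groups. It gives no other threshold.
- **Setting and sample size.** The calculation is made "with 95% confidence interval and 80% power of a test, 78 participants will be required". The printed formula uses 1.96 and 0.84 as its normal deviates and 0.4 and 0.2 as its two proportions, and it ends at 78.4. After an allowance of 10% for attrition, participants are to be "randomly allocated to the intervention group (*n* = 88) or the control group (*n* = 88".

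No other section states a significance threshold or corrects the sign.

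**The concern.** A 5% test treats a result as statistically significant when the p-value falls below 0.05. The analysis paragraph prints the opposite inequality, so it conflicts with the level on which the trial was sized. It also expresses alpha, which is a fixed number, as a range of p-values.

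A published protocol is the reference against which the results paper will be read. The threshold for the main between-group comparison should therefore be correct on the page, even where a reader can guess what was meant. This is not a detail left to a fuller document: the article states the threshold and states it wrongly.

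**Working it through.** **Inputs, all from Setting and sample size:** P1 = 0.40, P2 = 0.20, normal deviates 1.96 and 0.84, attrition 10%, equal allocation.

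**1. Reproduce the plan's figure.**

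n per group = (1.96 + 0.84)² × (0.4 × 0.6 + 0.2 × 0.8) / (0.4 − 0.2)²
= 7.84 × 0.40 / 0.04 = 78.4.

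This matches the article. Unrounded deviates (1.95996 and 0.84162) give 78.49. Rounded up, n is 79. Then 79 / (1 − 0.10) = 87.8, so 88 per group and 2 × 88 = 176 in total, as stated.

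**2. Which significance level does this imply?**

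2 × (1 − Φ(1.96)) = 0.050, which is two-sided 5%. A one-sided 5% test in the same formula would give 61.8 per group. Of these two, only the two-sided level leads to 78.4. The trial is therefore sized to reject when the two-sided p-value is below 0.05.

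**3. What the printed inequality would mean if applied literally** (an effect declared when p > 0.05).

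- No true effect: P(p > 0.05) = 1 − 0.05 = 0.95, in place of 0.05.
- Planned effect at the nominal power: P(p > 0.05) = 1 − 0.80 = 0.20, in place of 0.80.

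The second figure depends a little on the test and on the number analysed:

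| Participants per group | Test | Power when p < 0.05 is required | Chance of declaring an effect under the literal rule |
|---|---|---|---|
| 78 | unpooled | 79.8% | 20.2% |
| 79 | unpooled | 80.3% | 19.7% |
| 78 | pooled | 78.4% | 21.6% |
| 79 | pooled | 78.9% | 21.1% |
| 88 (no attrition) | pooled | 83.1% | 16.9% |

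About 20% is a fair summary, with a range of 17% to 22%.

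**4. Effect of the correction on the sample size.** None. The formula already uses two-sided alpha = 0.05, so 78.4, 88 and 176 all stand.

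**The case against.** The strongest reply is that this is a one-character slip with no practical consequence. The sentence sets an alpha level clumsily. It does not say that the intervention will be declared effective when p exceeds 0.05. Read with the sample-size section, it has one sensible meaning, a 5% level. This stands, and it is why the severity is minor. It does not remove the error, because the sentence is complete, it is the only threshold in the analysis paragraph, and it contradicts the other section.

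Four stronger readings are tempting, and the documents do not support them.

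- *The trial will count non-significant results as positive.* A reader might infer this from the 95% and 20% figures. Those figures describe the printed text taken literally. Nothing in the article suggests that the investigators intend it. The Background hypothesises a benefit over control, and the sample size assumes an ordinary 5% test.
- *Sidedness is undefined.* The analysis paragraph does not mention it, but 1.96 in the sample-size formula fixes it as two-sided. Restating it is useful; its absence from that paragraph is not a separate error. The subscript in the formula seems to have lost its slash in extraction and is not counted.
- *The sample-size arithmetic is wrong.* It reproduces at each step. The conflict lies between two sections, not inside the calculation.
- *The corrected rule should name a primary outcome, such as a safe-behaviour score at three months.* The article designates no such outcome. The Questionnaires section lists baseline, post-intervention and three-month measurements without ranking them, and the sample size is built on proportions, not on a score. Adding an endpoint here would settle a design question under cover of a typographical correction.

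**Conclusion.** Wrong as written, minor severity. The printed threshold has its inequality reversed and contradicts the two-sided 5% level behind the sample size. It is very probably a slip for p < 0.05.

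The literal consequence, a 95% type I error rate and about a 20% chance of declaring the planned difference, shows what the sentence says and is not a forecast of how the trial will be analysed. The 20% assumes the plan's own 40% versus 20% and its nominal 80% power. The conclusion that the intended level is two-sided 5% rests on the 1.96, the 95% confidence and the reproduced 78.4.

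**What to change.** In the analysis paragraph, replace the clause on alpha with: *Tests are two-sided at alpha = 0.05; p < 0.05 is considered statistically significant.*

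The cost is one sentence. The sample size stays at 88 per group and 176 in total, and no other part of the design or analysis changes. The correction should stop at the threshold and sidedness and should not add an outcome or a time point.

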**Methods:**

One hundred seventy-six workers will be recruited to this study from an Iranian petrochemical industry. The study is Mixed Methods Research (MMR) which will be carried out in two phases. In the first phase, using a qualitative approach, in-depth interviews will identify the causes of unsafe behaviour in the petrochemical industry. In the second phase, models of safe behaviour used in workplaces and the petrochemical industry will be investigated. The findings of the first phase will be matched with the constructs of these models to produce a well-suited conceptual model. Questionnaires and an educational intervention will be designed based on the results of the two phases. The workers will receive training interventions using direct methods, involving training sessions and workshops, and in an indirect method for which educational software will be designed. A randomised controlled trial (RCT) will assess comparability between the intervention group and the control group at baseline, after the intervention, and at a three-month follow up.

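### The questionnaire is collected at baseline and two later waves, but the stated effectiveness analysis gives the baseline score no role and does not use the two follow-up waves jointly

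*Protocol article*

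**What the plan says.** All references are to the protocol article.

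- **Data collected (Questionnaires).** "Data will be collected at baseline, after the intervention, and after three months for workers from the intervention group and the control group". The abstract's Methods paragraph matches this: the trial "will assess comparability between the intervention group and the control group at baseline, after the intervention, and at a three-month follow up".
- **Effectiveness analysis (analysis paragraph closing the Intervention section).** "Effectiveness of the intervention will be measured by the differences between the study groups (intervention group and control group". No model, covariate, time point or scale (follow-up score or change) is given.
- **Tests named (same paragraph).** "The difference of characteristics of participants will be compared by t test or chi-square 2 test or non-parametric equivalent test". The subject of this sentence is participant characteristics, not expressly the outcome.
- **Use of baseline (same paragraph).** "Descriptive statistics will be applied to describe the study population at baseline". This is the only use of baseline data that the paragraph states.
- **Linkage (Questionnaires).** "The questionnaires will be anonymous to promote participation and workers’ confidence in the intervention". No linking code is described.
- **Sample size (Setting and sample size).** A two-proportion formula, 40% against 20%, "with 95% confidence interval and 80% power of a test, 78 participants will be required", raised to 88 per arm for 10% attrition. The formula has no baseline term.

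**The concern.** The main research question asks whether safe behaviour is promoted and maintained. The design supplies what is needed to answer it efficiently: one pre-randomisation-type measurement and two later ones on the same instrument, in both arms. The analysis text uses this only as a between-group difference. It is specific elsewhere, naming the software, the two-group tests and path analysis for the conceptual model, but for the main question it gives the baseline score no role.

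Two things are at stake.

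- **Precision.** If a worker's baseline score predicts the later score, leaving it out gives a wider confidence interval and less power from the same 176 workers.
- **Choice after the fact.** Follow-up score, change score and baseline-adjusted score can give different answers, at either of two follow-up waves. As written, all of these fit the sentence.

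The linkage question makes the point worth settling before data collection. If baseline and follow-up questionnaires cannot be paired by worker, no later analysis plan can recover the adjustment.

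**Working it through.** **1. The plan's own figure.** From Setting and sample size:

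n = (1.96 + 0.84)² × (0.4 × 0.6 + 0.2 × 0.8) / (0.4 − 0.2)² = 7.84 × 0.40 / 0.04 = 78.4 per arm.

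Allowing for attrition, 78.4 / 0.9 = 87.1, so 88 per arm and 176 in total. The stated figures reproduce. With 10% loss, 88 × 0.9 = 79.2, so about 79 completers per arm.

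**2. Inputs for the comparison.**

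- From the article: two-sided alpha 0.05 (Z = 1.96), power 80%, 79 completers per arm.
- Assumed: the outcome is a continuous score. The sample size treats it as a proportion, so this departs from the article's own calculation.
- Assumed: a baseline to follow-up correlation r of 0 to 0.7. The article gives none, and the questionnaire is still to be designed.
- Derived: the effect size is anchored to the planned power. The standardised difference that gives an unadjusted two-sample t test 80% power with 79 per arm is 0.449 SD (noncentral t).

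**3. Formulas.**

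- SE of the unadjusted difference = √(2/79) = 0.159 SD.
- SE with baseline as covariate = 0.159 × √(1 − r²).
- Effective standardised difference = 0.449 / √(1 − r²), put into the noncentral t.
- For a change score, the variance factor is 2(1 − r) in place of 1 − r².

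**4. Results.**

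| r (assumed) | Variance factor 1 − r² | SE, adjusted (SD) | Power, unadjusted | Power, baseline-adjusted | Power, change score |
|---|---|---|---|---|---|
| 0 | 1.00 | 0.159 | 80% | 80% | 51% |
| 0.3 | 0.91 | 0.152 | 80% | 84% | 66% |
| 0.5 | 0.75 | 0.138 | 80% | 90% | 80% |
| 0.7 | 0.51 | 0.114 | 80% | 98% | 95% |

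The effect detectable with 80% power falls from 0.449 SD to 0.449 × √(1 − r²): 0.428, 0.389 and 0.321 SD at r = 0.3, 0.5 and 0.7.

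**5. Chance imbalance.** A baseline imbalance of one standard error (0.159 SD) shifts an unadjusted difference by r × 0.159, that is 0.05, 0.08 and 0.11 SD at r = 0.3, 0.5 and 0.7. The unadjusted standard error already allows for this on average. Adjustment removes it in the trial at hand.

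**The case against.** The strongest reply is that the article is silent, not wrong. The effectiveness sentence does not say unadjusted, and it is compatible with ANCOVA, a change score or a mixed model. This is a condensed article, and covariates are commonly fixed in a full protocol or analysis plan that is not shown. That part stands: a reader might infer that the plan commits to a raw comparison and discards the baseline score, but the text does not say so.

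A reader might also infer that the baseline score is used only for a significance test of balance. The documents do not support that either. The sentence naming the t test and chi-square test concerns participant characteristics. It plausibly means baseline testing, but it never says that the baseline outcome is tested.

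The reply adds that an unadjusted comparison would be no error. This is correct: under randomisation it is unbiased on average and keeps its nominal alpha. It is also true that the gain rests on an assumed r, is only about 4 percentage points at r = 0.3, and is nil at zero.

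What remains is that a baseline score is collected in both arms, the one stated effectiveness analysis gives it no role, and a better use of it is available at little cost. The anonymity statement also bears on whether any later plan could use it.

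**Conclusion.** The point holds as a matter of efficiency and pre-specification, not of validity. The article collects three waves in both arms and names no effectiveness analysis that uses the baseline score or takes the two follow-up waves together.

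If the comparison is in fact unadjusted, power at the planned effect is 80% where about 84% to 98% could be had, for r from 0.3 to 0.7. The variance is larger than it need be by a factor of 1/(1 − r²): 1.10 at r = 0.3, 1.33 at 0.5 and 1.96 at 0.7. These figures assume a continuous score, 79 completers per arm and linkable records. They illustrate a range and do not measure a loss in this trial.

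It would go too far to conclude that the trial is biased or that its test would be invalid. Confidence is moderate, because the analysis sentence is open to more than one reading and r is unknown.

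If the intended contrast is a change score, naming ANCOVA still matters. Across the tabulated correlations the change score has less power than ANCOVA, and below r = 0.5 it has less power than the plain follow-up comparison.

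**What to change.** Replace the effectiveness sentence with a named analysis of the safe-behaviour score. Either of these will do:

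- ANCOVA of the three-month score on arm, with the baseline score as covariate; or
- a linear mixed model of both follow-up waves with arm, wave, arm-by-wave and baseline score as covariate. This also addresses maintenance. The three-month contrast is read from it.

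Report the adjusted mean difference with its 95% CI. Describe baseline by arm in a table rather than by significance tests. State whether the outcome is a score or a proportion, since the sample size uses a proportion.

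The cost is one or two sentences, with no extra participants or measurements. The mixed model can be run in the SPSS version already named. The one practical downside is that the questionnaires must carry a pseudonymous study code, so that each worker's baseline and follow-up records can be linked. The anonymity statement in Questionnaires should be reworded to match, along with what workers are told about it.
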